#### Sample size estimation

2.2.1

The estimated sample size will be compared using 2 sets of odds ratios. The formula is as follows:$$n_{1}={\left[\frac{z_{1}-\alpha /2\sqrt{\bar{p}\bar{q}(1+1/r)}+z_{1}-\beta \sqrt{p_{1}q_{1}+p_{2}q_{2}/r}}{\Delta }\right]}^{2}=82$$

A total of 182 children were calculated using the transcript estimation method for the robustness of the clinical trial. The specific index is that α = 0.05 on both sides of the tail, and (1-β) is 0.80, and the absolute difference of the comprehensive result variable index is 20%. Our initial estimate of the sample size is 82, and the loss rate is increased by 10%, and 91 is determined for each group. Thus, the 2 groups totaled 182.^[13,14]^

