### Randomization and blinding

2.4

The staff member will refer to a specific random number handbook generated by an independent statistician based on statistical software before study activation to determine the study intervention assigned to the randomized patient. The randomization schedule is layered by the position of each 4-bit variable block. Participants will be randomly assigned to 1 of the 2 groups in a 1:1 ratio after completion of baseline assessment, according to a randomized block list generated by an independent research assistant using R, and the code will be kept in opaque sequentially numbered envelopes. The treatment allocation codes will be enclosed by an independent research assistant in sequentially numbered opaque envelopes and will not be revealed until the participants have completed all baseline assessments and immediately before the first massage treatment. The single-blind method is adopted in this study, and there are two-level blind methods. First, blind evaluation, in which the participants are evaluated by a third party who does not know the grouping. Second, the blind statistical analysis, where the statistical data will be analyzed by statisticians with unclear grouping and its meaning. (Fig. 1)

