**Figure 2 F2:**
[figure not shown]
Location of acupoints.

(1)Quality assurance of massage treatment(2)All operators conduct unified training and consistency check. Kappa value is greater than 0.8 to perform the above-mentioned massage operation independently.(3)Control group: basic rehabilitation treatment group

Basic rehabilitation treatment: All children will receive basic treatment according to the rehabilitation concept applied in the individual hospital and/or as demanded by the cost bearers. It will consist of physical factor therapy, occupational therapy, physiotherapy, and medical exercise.

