### Statistical analyses^[25]^

2.12

The primary analysis will be performed using intention-to-treat methods and therefore include all randomized child data. All data will be checked into the double machine using Epidata 3.1 software for database management.

Specific statistical analysis methods: The baseline characteristics of patients in the 2 groups will be reported using frequency distribution and descriptive statistics (including measurements of concentration trends and dispersion). The main analysis of the comprehensive measurement of the rate of counting data will be the chi-square test. Two independent samples of the *t*-test will be performed between the 2 groups. The paired t-test will be used to compare the outcome variables of each treatment group before and after the treatment. The difference between the multiple measurements of the same group will be conducted using the multiple measures data analysis of variance, combined with logistic regression analysis to examine the adjustment effect of clinically relevant covariates, which will be the results (gender, birth weight, gestational age). We will also follow the pre-specified subgroup analysis. All analyses will be performed using the R software. The aforementioned steps will be monitored by the third-party tests, and the quality control of the test will be carried out. The blind law is unified and responsible.

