## Discussion

3

The study protocol of the proposed trial will be conducted at the second affiliated hospital of the Yunnan University of Chinese Medicine. The present study is designed to investigate whether it is feasible, effective, and safe to use massage therapy for pediatric cerebral palsy patients with basic rehabilitation treatment. If successful, the study would provide useful information for integrating massage into rehabilitation care as part of the effort of integrating Chinese and Western medicine in mainland Chinese hospitals. However, this study protocol faces several challenges and limitations.

First, patients with different types of diagnosis of children with cerebral palsy will be included, which may create variability in the population. However, Chinese medicine treatment pays more attention to syndrome differentiation rather than diagnosing disease. Also, for younger children aged <3 years, diagnosis is challenging. Moreover, randomization will be rigorous for balancing the different types of spastic cerebral palsy in the 2 groups.

Second, since this trial only involves the efficacy of massage therapy based on basic rehabilitation therapy, whether massage and basic rehabilitation therapy will form an interaction or massage therapy can be used as an alternative therapy to basic rehabilitation therapy has not been considered.

Third, the quality control of the 4 centers is particularly important, including basic rehabilitation and quality control of massage therapy. Solving this problem relies mainly on continuous training and sincere cooperation of the central treatment team, as well as establishing good relationships with the patient's family to increase compliance and follow-up.

Fourth, the choice of the control group is a difficult point in this study, although this trial is most likely to verify the clinical efficacy of massage therapy.

Currently, we cannot provide an estimate for the massage treatment costs for the treatment and control groups. It is assumed that this study can provide evidence of efficacy and high quality for the rehabilitation of cerebral palsy in children with rehabilitation and useful information for future health economic analysis. We also presume our findings to enhance the knowledge of the effectiveness of massage therapy in the hospital daily comprehensive medical practice.

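### The between-group tests are unadjusted although every outcome has a baseline value; adjusting for baseline score and centre would gain precision at no cost

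*Protocol article*

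**What the plan says.** Section 2.12 sets out the tests. Between arms it says "Two independent samples of the *t*-test will be performed between the 2 groups", and it gives a chi-square test, which it calls the main analysis, for a rate. No covariate is attached to either. The paired t-tests compare before and after within each arm. The repeated-measures analysis of variance is described for measurements of the same group, so it is not presented as a treatment comparison. Adjustment appears once, as a logistic regression with three covariates: sex, birth weight and gestational age. The section does not say whether the t-test is on week-12 scores or on changes from baseline.

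Other sections show what is available for adjustment:

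- Section 2.6.1: all outcomes are measured before enrolment and at the end of weeks 4, 8 and 12.
- Section 2.4: "Participants will be randomly assigned to 1 of the 2 groups in a 1:1 ratio after completion of baseline assessment".
- Section 2.3: eligibility requires age 1 to 3 years and gross motor function level I to III, so both are known for every child.
- Section 2.5: basic rehabilitation is given "according to the rehabilitation concept applied in the individual hospital and/or as demanded by the cost bearers". The Discussion counts 4 centres.
- Section 2.4, on the structure of the randomisation list: "The randomization schedule is layered by the position of each 4-bit variable block".

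**The concern.** The baseline value of each score is recorded and then left out of the between-group test. If it correlates with the week-12 value, part of the spread within each arm can be explained before treatment starts. An unadjusted test counts that part as noise. Centre is similar: the protocol itself says that background treatment differs by hospital, so centre may carry outcome variance, and it appears nowhere in the analysis.

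The adjustment that is planned does not fill the gap. It omits baseline score, centre, age and function level, and a logistic regression does not apply to a GMFM score or to Ashworth points unless they are dichotomised.

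What is at stake is power and the width of the confidence interval, and how a chance difference between arms in baseline function is handled. The protocol states its tests and lists its covariates, so this is a choice it makes and not a detail it leaves open.

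**Working it through.** **Inputs from the protocol (Section 2.2.1).** Significance level: "The specific index is that α = 0.05 on both sides of the tail". Power: 0.80. Effect: "the absolute difference of the comprehensive result variable index is 20" per cent. Size: "Our initial estimate of the sample size is 82, and the loss rate is increased by 10%, and 91 is determined for each group".

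**Reproducing the stated size.** The two rates are not given. With 60% against 80% (or the mirror pair, 20% against 40%) and the two-proportion formula without continuity correction:

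n = [(1.960·√(2·0.70·0.30) + 0.842·√(0.60·0.40 + 0.80·0.20)) / 0.20]² = 81.2, rounded up to 82.

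Then 82 × 1.1 = 90.2, rounded up to 91 per arm and 182 in total. The stated figures reproduce, and 82 per arm is used below.

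**Assumed inputs.** The protocol gives no standardised difference (SMD) for the scores and no baseline-to-week-12 correlation r. I take SMD = 0.30 and r = 0.3, 0.5, 0.7 and 0.8, with equal variances at the two times.

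**Formulas.** Relative to a week-12 t-test, the residual variance is 1 − r² for ANCOVA and 2(1 − r) for a t-test on change. Power is from the non-central t distribution with 82 per arm and effective SMD = 0.30/√(variance factor).

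| r | ANCOVA factor | Change factor | Week-12 t-test | Change t-test | ANCOVA |
|---|---|---|---|---|---|
| 0.3 | 0.91 | 1.40 | 48.0% | 36.5% | 51.7% |
| 0.5 | 0.75 | 1.00 | 48.0% | 48.0% | 59.7% |
| 0.7 | 0.51 | 0.60 | 48.0% | 69.3% | 76.2% |
| 0.8 | 0.36 | 0.40 | 48.0% | 85.5% | 88.9% |

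A normal approximation gives 37% for the change-score test at r = 0.3. The other cells move by about half a point or less.

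The ordering does not depend on the SMD. The ratio of the ANCOVA to the change-score variance is (1 − r²)/(2(1 − r)) = (1 + r)/2, which is below 1 for every r below 1.

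**A second anchor.** The SMD that a week-12 t-test detects with 80% power at 82 per arm is (1.960 + 0.842)·√(2/82) = 0.438. At that SMD, by normal approximation, ANCOVA has 83.6%, 89.9%, 97.5% and 99.7% power for the same four values of r. The change-score test has 65.8%, 80.0%, 95.1% and 99.3%. The size per arm that ANCOVA needs for 80% power is 82 × (1 − r²), that is 75, 62, 42 and 30.

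**Centre.** Let the intraclass correlation (ICC) be the share of outcome variance between centres; the protocol gives none, so 0.02 to 0.20 is assumed. If allocation is balanced within centre, the true standard error is smaller by √(1 − ICC) than the one the unadjusted test uses. The actual two-sided type I error is 2[1 − Φ(1.960/√(1 − ICC))]: 0.048, 0.044, 0.039 and 0.028 at ICC 0.02, 0.05, 0.10 and 0.20. At SMD 0.438, power is 80.2%, 80.6%, 81.3% and 82.7% unadjusted, against 80.8%, 82.0%, 84.0% and 87.9% with centre in the model. The cost is about 0.6 to 5 points.

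**The case against.** **Nothing here is invalid.** Under randomisation the two-sample t-test is unbiased, and chance baseline imbalance is already allowed for in its error rate. The trial also calls itself a pilot. This stands: the point concerns efficiency. A reader might infer that leaving out baseline score or centre biases the result or inflates false positives. The documents do not support that. If allocation is balanced within centre, the effect is in the conservative direction.

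**The gain depends on an unstated reading and on assumed inputs.** If the t-test is on change, the gain from ANCOVA at r = 0.7 and 0.8 is about 7 and 3 points, not 28 and 41. At r = 0.3, ANCOVA adds only about 4 points over a week-12 t-test. This also stands, and it is why both readings and the range of r are shown.

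**The test called main is the chi-square test.** The power figures above do not apply to it. It is unadjusted too, so the recommendation extends to it without those figures.

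**The stratification sentence is unclear.** A reader might take its wording to mean stratification by site and conclude outright that the t-test's standard error is too large. The sentence is too garbled for that, so the statement is conditional. The case for including centre rests on the hospital-specific background treatment.

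**Palsy type and missing visits.** The Discussion says that "randomization will be rigorous for balancing the different types of spastic cerebral palsy in the 2 groups", and a reader might want palsy type as a covariate as well. No section shows that subtype is recorded, so it is not proposed. Nor does the intention-to-treat statement require a mixed model; that is one suitable option.

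**Conclusion.** The point holds as a loss of precision. The protocol fixes unadjusted between-group tests and a short covariate list that omits the baseline score and centre, although both are available for every child.

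The size is uncertain because the protocol gives neither r nor an SMD. At SMD 0.30 with 82 per arm, adding the baseline score gains roughly 4 to 41 power points over a week-12 t-test as r goes from 0.3 to 0.8. Over a change-score t-test it gains roughly 15 points at r = 0.3, falling to 3 at r = 0.8. ANCOVA is ahead on either reading. Leaving out centre costs less, about 0.6 to 5 points over the assumed ICC range, and makes the t-test somewhat conservative only if allocation is in fact balanced within centre.

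The documents give no correlations for age or gross motor function level, so no gain is claimed for them. They are sensible covariates because they are known from eligibility. This should be changed, but the trial is valid without it.

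**What to change.** In Section 2.12, replace the between-group t-test with this: the GMFM and Ashworth scores at week 12 are compared by ANCOVA, or by a mixed model over weeks 4, 8 and 12 with the week-12 contrast as the estimate. The model contains treatment, the baseline value of the same score, centre, age and gross motor function level. For any rate, replace the chi-square test as the main comparison with a logistic regression on treatment, the corresponding baseline score and centre. State in Section 2.4 whether the randomisation is stratified by centre.

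The cost is wording. Baseline scores, age and function level are already collected and centre is known, so no extra children, visits or measurements are needed. The article says that recruitment is still under way, so the change can be recorded before any unblinded analysis.

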**Methods/Design::**

The study will be a multicenter, single-blinded, randomized-controlled pilot trial. During the period from June 2019 to December 2020, 182 children with spastic cerebral palsy will be randomly divided into experimental and control groups in a 1:1 ratio. The experimental group will undergo the modified selective spinal massage method combined with the basic rehabilitation treatment, while only the basic rehabilitation treatment would be performed for the control group. The intervention period of the study will last 12 weeks, 5 days weekly on weekdays. The primary outcomes include a modified Ashworth scale assessment and gross motor function test. The secondary outcomes include the 4-diagnostic scale of Chinese medicine and children's intelligence. The observation index will be measured during the complete 12 weeks duration after the treatment of the child, that is, before treatment, after 4 weeks of treatment, after 8 weeks, and after 12 weeks of treatment.

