### Subject recruitment

2.3

Inclusion criteria:

(1)Aged 1 to 3 years, both male and female children.(2)Grading of the large motor function at the I-III level.^[15,16]^(3)Children who meet the diagnostic criteria for spastic cerebral palsy.^[17]^(4)Muscle tone between I-IV (according to the newly revised Ashworth scale).(5)Follow the doctor advice during the study and insist on receiving the tester.

Exclusion criteria:

(1)Those with severe mental illness and severe epilepsy.(2)Organized diseases involving other organs such as the heart, liver, and kidney.(3)Exclusion of leukodystrophy, infantile spinal muscular atrophy, spin cerebellar ataxia, genetic metabolic diseases such as phenylketonuria, congenital cretinism, and congenital hydrocephalus.(4)Failure to meet the inclusion criteria, failure to complete the test according to the regulations, and the treatment of patients who have an influence on the test results during the study, the incomplete data affect the clinical efficacy observation.(5)Spontaneous bleeding tendency.

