#### Outcome assessment

2.6.1

All the outcomes will be measured before enrollment, at the end of 4 weeks, the end of 8 weeks, and the end of 12 weeks follow-up. The summer of all the measures in the trial is shown in Figure 3. (Fig. 3)

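### The only before-after and repeated-measures analyses in the plan are within each arm, so they cannot estimate massage against control

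*Protocol article*

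**What the plan says.** Section 2.12 (Statistical analyses) names four tests that bear on this point.

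- Between groups, for a rate: "The main analysis of the comprehensive measurement of the rate of counting data will be the chi-square test".
- Between groups, presumably for continuous scores: "Two independent samples of the *t*-test will be performed between the 2 groups". The visit is not stated, nor whether raw scores or changes are compared.
- Before versus after: "The paired t-test will be used to compare the outcome variables of each treatment group before and after the treatment".
- Repeated visits: "The difference between the multiple measurements of the same group will be conducted using the multiple measures data analysis of variance". The same sentence adds a logistic regression for covariates (sex, birth weight, gestational age), with no visit term mentioned.

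The setting is given elsewhere. The abstract says "The primary outcomes include a modified Ashworth scale assessment and gross motor function test". Under Outcome assessment (2.6.1), outcomes are "measured before enrollment, at the end of 4 weeks, the end of 8 weeks, and the end of 12 weeks". The first inclusion criterion in 2.3 is "Aged 1 to 3 years, both male and female children". On background care, the treatment section says "All children will receive basic treatment according to the rehabilitation concept applied in the individual hospital".

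**The concern.** The trial asks whether massage adds anything to basic rehabilitation. A paired test within one arm asks whether that arm's mean changed, and so does a repeated-measures ANOVA within one arm. The change being tested mixes any massage effect with rehabilitation, development, regression to the mean and practice at the test. Only a comparison with the randomised control arm separates these.

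The mixture matters here. GMFM and the Bayley scale measure abilities that are still developing at 1 to 3 years, and both arms receive rehabilitation for 12 weeks. Some gain without massage is therefore plausible on these scales. It is less clear for the Ashworth score, where rehabilitation or regression to the mean is the likelier source.

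Two things are at stake. A significant within-arm test could be presented as evidence for massage when massage does nothing. And the four-visit data, as planned, are analysed jointly only within arms, so the one method that uses all visits does not address the trial's question.

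**Working it through.** **Inputs from the documents.** Two-sided α = 0.05, power 0.80, a 20-point difference, 82 per group before loss and 91 after a 10% allowance (2.2.1); four measurement times (2.6.1). Not given: the two rates, and any expected change, SD or correlation between visits. These are assumed below.

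**The plan's own figure.** With assumed rates of 60% and 80% (mean 70%), the formula in 2.2.1 gives

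n = [(1.960·√(2·0.7·0.3) + 0.842·√(0.6·0.4 + 0.8·0.2)) / 0.20]² ≈ 81.2, rounded up to 82.

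Then 82 × 1.1 = 90.2, rounded up to 91 per group and 182 in total. The stated size reproduces. It rests on comparing two rates and does not depend on the present point. I use 82 per arm, the number before the loss allowance.

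**Paired t-test with no massage effect.** Let both arms have the same true mean change, δ SDs of the change score. The paired statistic in an arm is noncentral t with 81 degrees of freedom and noncentrality δ√82, and the critical value is 1.990. Let p be the probability of significant improvement in one arm. The arms are independent, so significance with massage but not with control has probability p(1 − p).

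| Common change δ | δ√82 | p | p(1 − p) | Simulated p | Simulated massage only | Simulated between-group t-test |
|---|---|---|---|---|---|---|
| 0 | 0 | 0.025 | 0.024 | 0.025 | 0.025 | 0.048 |
| 0.1 | 0.91 | 0.143 | 0.123 | 0.145 | 0.124 | 0.050 |
| 0.2 | 1.81 | 0.432 | 0.245 | 0.434 | 0.245 | 0.051 |
| 0.3 | 2.72 | 0.766 | 0.180 | 0.771 | 0.182 | 0.048 |
| 0.5 | 4.53 | 0.994 | 0.006 | 0.995 | 0.006 | 0.052 |

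The simulation used 20,000 trials per row. Its last column is a two-sample t-test on change scores, which rejects about 5% of the time whatever the common change. About half of those rejections, 2.5% of trials, favour massage.

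The two within-arm risks peak in different places. Discordance in favour of massage is highest, near 25%, when p is close to 0.5, and almost vanishes at 0.5 SD. By then the massage-arm test is significant nearly every time.

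**Within-arm repeated-measures ANOVA.** Assumptions: four visits, 82 children, linear change, correlation 0.8 between visits, and change expressed in SDs of the raw score. It rejects in 5% of 3,000 simulated trials at zero change, and in 22%, 70% and 98% at 0.1, 0.2 and 0.3 SD, again with no massage effect.

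**The case against.** The strongest reply is that the plan does contain randomised comparisons. The chi-square test is called the main analysis and the two-sample t-test is between groups. A reader might infer that the four-visit data never enter a randomised comparison. The text does not support that: the t-test could be run at 4, 8 and 12 weeks or on change from baseline, because neither visit nor scale is fixed. What stands is narrower. No between-group analysis using the visits jointly is named, and the repeated-measures method that is named is confined to one group.

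Second, nothing in the article says that efficacy will be concluded from within-arm tests. That is correct, so the invalid claim is a risk and not a stated intention. But the tests are planned as significance tests beside the between-group ones, and nothing bars such use.

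Third, a reader might infer that these tests will show improvement from normal development alone. That goes too far. No expected gain is given, both arms receive rehabilitation, and development is a weak explanation for change in muscle tone.

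Fourth, any single probability can be chosen to look alarming, since p(1 − p) cannot exceed 25%. Hence the range above.

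Finally, a longitudinal model is not the only valid remedy. A baseline-adjusted or change-score comparison at 12 weeks would also give a randomised contrast. That is fair, but it would leave the within-group ANOVA as the only analysis using all the visits together.

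**Conclusion.** The point holds in its limited form. The paired t-test and the repeated-measures ANOVA, as specified, do not estimate massage versus control and can be significant when massage has no effect. With 82 per arm, two-sided 5% tests and an equal change in both arms of 0.1 to 0.5 SD of the change score, the massage-arm paired test is significant in about 15% to 99% of trials. The pattern of significance with massage but not with control appears in about 1% to 25%. A between-group test stays near 5%, with about 2.5% in massage's favour. The sizes depend on the assumed change, but the within-arm design of the two analyses is plain from the wording. This is a worthwhile correction to the analysis section. It does not show that the trial lacks a between-group test, and the sample size is unaffected.

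**What to change.** In section 2.12:

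1. Replace the within-group repeated-measures ANOVA with one between-group longitudinal model for each continuous outcome, with group, visit, group-by-visit and baseline value, and name the 12-week between-group contrast as the estimate of interest.
2. Report within-arm change as mean and SD by visit, without significance tests, or label any retained paired test as descriptive.
3. State that efficacy conclusions will be drawn only from between-group contrasts.

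The cost is analysis wording. The baseline and the 4-, 8- and 12-week measurements are already planned, so no extra children, visits or assessments are needed.
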